For the investigation of the scope of WM, the second block of the eye-tracking experiment will follow the standard dual-task design, in which speakers are first asked to memorize a list of words, then describe a picture of simple transitive actions, and finally to recall the memorized list of words [14, 15, 29, 31, 35, 66]. Before seeing a picture, speakers are shown three nouns semantically unrelated to the action in the picture and asked to remember these words (e.g., traditsioon, ‘tradition’, otsing, ‘search’, investor, ‘investor’). The conceptual load is tested by the so-called verb probe task, which means that after describing the picture, the participants are prompted with a verb, for which they are requested to orally recall the three nouns and to indicate whether they all fit with the verb on the screen (see procedures in [29] for the modification of the standard WM task to tap the phonological and semantic retention). For example, the nouns ‘tradition’, ‘search’ and ‘investor’ co-occur and are acceptable with a transitive verb ‘jätkama’ in Estonian (according to the frequency counts in the National Estonian Corpus and the previous norming study). Crucially, the verb probe task is expected to tap the conceptual retention and deteriorate the conceptual planning processes in describing the pictures such that speakers spare time on making the higher-level conceptual decisions and proceed with describing the pictures in a more incremental manner. This means that instead of previewing and conceptualizing all actors in the pictures, speakers will preview and conceptualize only the actors they mention first in their picture descriptions.

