The eye movements in the existing studies are typically investigated as continuously changing functions of time in a fixed time window (from 0 to 400/600/1000 ms of picture presentation) [16–21, 69, 70]. For the purposes of this study, we derive a new relative measure from the eye movements based on what is currently known about eye movement in the linguistic task settings [16–21, 25, 69, 70]. The new metric is based on the notion of gaze that is defined as multiple consecutive fixations directed towards the region of interest [72]. As the clear start of phonological processing is indexed by a long and intense gaze towards the first-mentioned actor/object right before the onset of speech, the new measure takes this long, “naming” gaze as a landmark for the time window between the picture onset and the start of an utterance. In other words, the duration of these naming gazes will be divided by the speech onset latencies based on the following reasoning.

Namely, the time before the naming gaze indexes the time window where the conceptual frame of an incipient sentence is generated. The time after this longest gaze indicates encoding of further aspects of the incipient sentence (possibly the verb or second-mentioned actor). The highly incremental processing entails that after the picture onset, speakers start to encode the first-mentioned actors as soon as possible [18, 36, 69]. Since they might also start their speech early, they may spend most of the time period between the picture onset and the start of an utterance with processing the first-mentioned actors. In other words, the duration of the naming gaze at the first-mentioned actor relative to the speech onset latency is comparably high. Conversely, the weakly incremental planning assumes that speakers also take time for processing second-mentioned actors, such that the naming gaze at the first-mentioned actor starts later [16, 19] and the speech onset may be somewhat delayed. This means that the duration of the longest gaze towards the first-mentioned actor relative to the speech onset latency is rather low. Consequently, the degree of incrementality and the effect of cognitive load on conceptual processing can be inferred from the duration of the naming gaze measured proportionally to the speech onset latency. In particular, the increasing proportional duration of the naming gaze at the first-mentioned actor or object approximates the increase of incrementality in the conceptual planning processes.

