### Hypotheses

In line with earlier studies, active sentences uttered in response to complex visual scenes are assumed to be produced less rather than more incrementally [15, 32, 35, 65, 76]. Oppermann et al. [76] show for German that sentences with a frequent subject-verb-object ordering (e.g., ‘Die Maus frisst den Käse’, ‘The mouse is eating the cheese’) can be successfully planned in full even at the phonological planning stage. For English, Ferreira and Swets [35] similarly demonstrate that speakers plan their active sentences non-incrementally when no time constraint is imposed. Therefore, this study of Estonian assumes that the conceptual planning under low cognitive load is only weakly incremental or even non-incremental, but it is expected to become more incremental when additional cognitive load is imposed, i.e., under high cognitive load. In other words, if conceptual planning processes share resources with WM, then the detrimental effect of high cognitive load should show increase in the incrementality of conceptual planning. The effect of cognitive load on the incrementality should be observable in the increased proportional duration of the naming gaze at the actor first mentioned before the onset of speech.

As argued in the previous paragraph, sentence planning is expected to proceed weakly incrementally or even non-incrementally under low cognitive load. Accordingly, tonal variation is expected to be determined by the number of concepts maintained in the WM or by sentence length such that sentence-initial intonation peaks are higher in longer than shorter sentences. The high cognitive load and the incrementality of planning are predicted to be tightly interrelated with the advance planning of sentence intonation. First, the incrementality is expected to relate to low pitch peaks because the highly incremental conceptualization processes only foresee mentioning the first concept in subsequent utterances. Second, the cognitive load is predicted to increase the sentence-initial pitch peaks given that the mental load arising from maintaining a complex conceptual network in WM (as it may occur whilst planning long but not short sentences) is comparable to the mental load that emerges from memorizing a word list. Consequently, two different outcomes of the load manipulation on sentence-initial intonation peaks are possible (see Fig 1).

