#### Dependent variables

The dependent variables of interest are (i) speech onset latencies, (ii) duration of naming gazes, (iii) duration of naming gazes proportional to their respective speech onset latencies, (iv) the height of sentence-initial pitch peaks as indexed by F0 maxima (v) and the height of sentence-final pitch valleys as indexed by F0 minima.

First, the starts of utterances (in milliseconds) index the speech onset latencies. Second, a gaze is defined as multiple consecutive fixations directed at the AOI [72]. Gaze duration is calculated by subtracting the onset time of the first fixation directed at the AOI from the offset time of the last consecutive fixation directed to the AOI. Typically, before the speech onset, between one and five gazes occur (see Fig 5). The number of gazes usually increases together with the complexity of the visual scene. The data analysis algorithm will compare between the durations of the gazes occurring before the speech onsets and determine the gaze with the maximum duration, i.e., the longest gaze. The naming gaze is reported as missing (NA) when, in the very unlikely case of only one gaze or of two gazes of exactly the same duration, the algorithm cannot detect a gaze with the maximum duration. The longest gaze before the speech onset is called the naming gaze and submitted to further analyses together with its AOI (either agent or patient).

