**Fig 5 pone.0259343.g005:**
[figure not shown]
Hypothetical onset latencies (left edge of bars) and duration (widths of bars) of gazes directed to a particular area of interest (e.g., blue refers to the agent initiating and orange to the patient undergoing the action of pulling) during the description of an item ‘man pulling a donkey’ in Estonian. The numbers on the squares count the gazes. The black vertical line indicates the speech onset latency. The red ellipse highlights the gaze that is called ‘naming gaze’ and defined as a gaze of longest duration prior to the start of an utterance. For assessing the degree of incrementality, the duration of the naming gaze is divided by the speech onset latency (for similar analysis procedures and data see, e.g., [19]).

Finally, F0 maxima and F0 minima are automatically extracted within the boundaries of agent and patient names and the boundaries of sentence-final words in cases where patient names do not occur at the end of a sentence (e.g., some sentence modifier (e.g., varsti, ‘soon’) follows the patient name). F0 maxima and minima measured in hertz (Hz) will be converted into semitones relative to speaker means based on Eq (1)
$$\begin{array}{c} F0_{st}=12*log_{2}\left(\frac{F0_{Hz}}{F0_{mean}}\right), \end{array}$$
(1)
where *F*0_*mean*_ is the subject’s mean F0 aggregated over all F0 contours extracted from all of the subject’s utterances. This method of converting F0 into semitones has the benefit of partly cancelling out the large-scale, gender-based differences in voice pitch (males typically have lower voice pitch than females). The effect of sentence length on sentence-initial pitch peaks is expected to be smaller than the gender effect. When gender variation in voice pitch is included in the data, the critical effects of sentence length and WM may remain unrevealed.

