#### Statistical analysis

The goal of the statistical analyses is to determine whether the scaling of sentence-initial pitch peaks in long sentences is affected by an independent effect of incrementality or by the simultaneous effects of incrementality and high mental load. As the manipulations of the factors Double Actor (agent vs patient) and Identity (same vs different) elicit short and long sentences (see in Materials), the combinations of these are reduced into a factor Sentence Length (short vs long) for the main analysis. Thus, the main analysis examines the effect of the interaction between Cognitive Load (low vs high) and Sentence Length (short vs long) on (i) the proportional duration of naming gazes at the first-mentioned actors, (ii) duration of naming gazes, (iii) the sentence-final pitch valleys, (iv) and the sentence-initial pitch peaks.

The four dependent variables (duration of naming gazes, proportional gaze durations, sentence-final F0 minima, sentence-initial F0 maxima) are modelled with separate linear mixed-effects regression analyses (LMER, as implemented in the *lme4* package in [82, 85]). All models include the interaction between Cognitive Load (low vs high) and Sentence Length (short vs long) as the fixed effect, the block and trial number as the covariate effects, and random intercepts and slopes for items and subjects. The analysis will be carried out using sum-to-zero coding of the fixed effects. To avoid the convergence issues, the models will be optimized following the procedures suggested in Bates et al. [82]. First, the continuous variables block and trial are centred and/or scaled for the statistical analyses. Second, the convergence tolerances are adjusted by applying an optimizing algorithm diverging from the standard test but which results in the converging model. Third, and only in case the previous measures do not yield the convergence of the model fit, the random effects structure will be simplified by removing the correlations term from the random effects structure. Finally, the significances of the model estimates are obtained with the help of the *lmerTest* package [86] in R [85]. The significances of the main effects and the interaction are determined at the threshold of p<0.05.

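### The algorithm takes the longest gaze at either actor as the naming gaze, but the incrementality outcome is meant for the first-mentioned actor; under the protocol's own hypothesis the mismatch would shrink the load effect in analysis 1

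*Protocol article*

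**What the plan says.** Three parts of the protocol article bear on this measure.

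- **Rationale** (Theoretical assumptions of the new measure of cognitive difficulty). Incrementality is the gaze at the first-mentioned actor relative to speech onset latency. Of less incremental planning it says "the weakly incremental planning assumes that speakers also take time for processing second-mentioned actors", with the result that "the duration of the longest gaze towards the first-mentioned actor relative to the speech onset latency is rather low".
- **Algorithm** (Dependent variables). All gazes before speech are compared and the longest is taken, whichever role it falls on: "The longest gaze before the speech onset is called the naming gaze and submitted to further analyses together with its AOI". The legend of Fig 5 repeats this: "defined as a gaze of longest duration prior to the start of an utterance". Neither requires the gaze to be on the first-mentioned actor.
- **Analysis** (Statistical analysis). The first two outcomes are "the proportional duration of naming gazes at the first-mentioned actors, (ii) duration of naming gazes". The first is tied to the first-mentioned actor. The second carries no such limit in that list. The first exploratory analysis reuses the proportional measure.

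The missing-value rule for the naming gaze covers only a single gaze or an exact tie. The eye-movement exclusions concern a late first fixation and long gaps between fixations. The section on pre-processing plans no treatment of missing data.

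**The concern.** The algorithm and the outcome agree only when the longest gaze is on the first-mentioned actor. Otherwise the algorithm returns a gaze that the outcome does not describe, and the analyst has two ways to proceed.

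- **Drop the trial from analysis 1.** Whether a trial is analysed then depends on how long the first-mentioned actor was viewed compared with the other, which is close to the outcome itself. A mixed model tolerates unbalanced data, but that does not repair selection on the outcome.
- **Keep the trial with its longest gaze.** A long look at the other actor then counts as high incrementality, although the rationale treats time spent on that actor as a sign of weak incrementality.

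Analysis 1 is the check that the verb probe task disturbed conceptual planning. If it comes out falsely weak, the pitch-peak results are harder to interpret in terms of incrementality.

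**Working it through.** **Step 1: which trials are affected.** The Hypotheses section expects that "the conceptual planning under low cognitive load is only weakly incremental or even non-incremental". The section on the speech production task expects that, with the verb probe, "speakers will preview and conceptualize only the actors they mention first in their picture descriptions". Together with the rationale above, this suggests that trials with the longest gaze on the other actor occur more often under low load. That is an inference; the protocol does not state it.

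**Step 2: set-up.** The plan gives no figure to reproduce: no share of affected trials, no expected load effect and no SD for the gaze proportion. All inputs below are assumptions. Let F and S be the longest pre-speech gazes at the first- and second-mentioned actor, each divided by speech onset latency. They are drawn from a bivariate normal distribution and clipped to 0–1, with 2 million trials per load level. The load effect is the high-load mean minus the low-load mean of:

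- fixed measure: F in all trials;
- kept: max(F, S) in all trials;
- dropped: F in trials with F > S only.

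**Step 3: one case in full.** F rises from 0.42 to 0.47 (SD 0.15), S falls from 0.30 to 0.27 (SD 0.12), correlation −0.5. The longest gaze is elsewhere in 30% of low-load and 20% of high-load trials.

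- Fixed: 0.470 − 0.420 = 0.050.
- Kept: 0.496 − 0.466 = 0.030.
- Dropped: 0.516 − 0.488 = 0.029 before rounding of the means.

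Keeping raises the low-load mean by 0.046 and the high-load mean by 0.026. Dropping raises them by 0.068 and 0.046. The low-load mean rises more each time, so the difference shrinks.

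**Step 4: range when load shifts gaze and latency is unchanged.** The true effect is 0.050 in every row.

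| F low→high | S low→high | SD of F, S | Correlation | Elsewhere, low / high | Kept | Dropped |
|---|---|---|---|---|---|---|
| 0.55→0.60 | 0.20→0.17 | 0.12, 0.10 | −0.5 | 3.3% / 1.2% | 0.048 (97%) | 0.045 (90%) |
| 0.55→0.60 | 0.20→0.17 | 0.15, 0.12 | −0.5 | 6.8% / 3.3% | 0.046 (92%) | 0.041 (83%) |
| 0.40→0.45 | 0.25→0.20 | 0.12, 0.12 | 0 | 19% / 7% | 0.038 (76%) | 0.034 (68%) |
| 0.42→0.47 | 0.30→0.27 | 0.15, 0.12 | −0.5 | 30% / 20% | 0.030 (60%) | 0.029 (58%) |
| 0.35→0.40 | 0.30→0.25 | 0.12, 0.12 | −0.6 | 41% / 24% | 0.018 (36%) | 0.024 (48%) |

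**Step 5: cases without shrinkage.** If load only shortens latency, so that both shares rise by 10% with no shift between actors, the effects are 0.040 (fixed), 0.041 (kept) and 0.043 (dropped). If load acts only on trials already longest on the first-mentioned actor, dropping gives 0.050 against 0.041 under the fixed measure, and keeping gives 0.041.

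**The case against.** The strongest reply is that the rationale already states the right measure, that the AOI is stored with each gaze, and that outcome (i) names the first-mentioned actor. On that view the algorithm and the Fig 5 legend are loosely worded, and no bad option has been chosen. Part of this stands: the remedy is to align the algorithm with the plan's own definition. But the algorithm is spelled out. Restricting its output to the first-mentioned actor by the stored AOI is the drop option, and it does not give the measure in the rationale.

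A reader might also infer that the protocol itself says weakly incremental trials have their longest gaze on the second-mentioned actor. It does not. It says that the gaze at the first-mentioned actor starts later and is proportionally shorter, and it describes a long gaze at that actor before speech as the usual pattern. Affected trials may therefore be few. They need not be, because actors sharing a role are enclosed in one AOI. Consecutive fixations across two patients count as one gaze, which can lengthen it. No frequency is given either way.

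A further tempting reading is that the load effect is biased towards zero whatever happens. Step 5 shows otherwise, and the rationale itself notes that incremental speakers may start speaking early, which is the latency route.

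Nor can it be said that no convention exists. The Fig 5 legend points to a cited study for similar procedures, which is not available here.

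**Conclusion.** The point holds in a limited form. The mismatch between the algorithm and the outcome is in the text, and no rule in the article resolves it. Shrinkage of the load effect is conditional: it needs high load to move viewing towards the first-mentioned actor, as the protocol hypothesises, and not to act mainly by shortening latency. Under that condition the loss in the assumed scenarios ran from 3–10% when few trials were affected to more than half when about 40% of low-load trials were. These figures are illustrative, since the documents give none of the inputs.

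The consequence is confined to analysis 1 and the first exploratory analysis. Analysis 2 uses the same naming gaze, so its AOI should be stated too. The pitch-peak and pitch-valley outcomes do not depend on the naming gaze and are unaffected. The change should be made before extraction, but it does not put the whole design in doubt.

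**What to change.** Rewrite the algorithm under Dependent variables, and the Fig 5 legend, to match the rationale. In every eligible trial the outcome is the longest pre-speech gaze at the AOI of the first-mentioned actor, divided by speech onset latency. No trial is dropped because of where the overall longest gaze fell. Restate the missing-value rule for single and tied gazes in the same terms.

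Score a trial as 0 when the first-mentioned actor is not fixated before speech, and give a sensitivity analysis with and without those trials. Report by load the share of trials whose longest gaze is elsewhere.

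The work is small: the AOI is already recorded, and first mention follows from the planned transcription and tagging. There are two real costs. Small or zero values make the distribution less regular for a linear mixed model. In some trials the gaze used may be a brief preview and not a true naming gaze; the reported share of trials with the longest gaze elsewhere shows in how many trials this could arise.

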**Fig 5 pone.0259343.g005:**
[figure not shown]
Hypothetical onset latencies (left edge of bars) and duration (widths of bars) of gazes directed to a particular area of interest (e.g., blue refers to the agent initiating and orange to the patient undergoing the action of pulling) during the description of an item ‘man pulling a donkey’ in Estonian. The numbers on the squares count the gazes. The black vertical line indicates the speech onset latency. The red ellipse highlights the gaze that is called ‘naming gaze’ and defined as a gaze of longest duration prior to the start of an utterance. For assessing the degree of incrementality, the duration of the naming gaze is divided by the speech onset latency (for similar analysis procedures and data see, e.g., [19]).

Finally, F0 maxima and F0 minima are automatically extracted within the boundaries of agent and patient names and the boundaries of sentence-final words in cases where patient names do not occur at the end of a sentence (e.g., some sentence modifier (e.g., varsti, ‘soon’) follows the patient name). F0 maxima and minima measured in hertz (Hz) will be converted into semitones relative to speaker means based on Eq (1)
$$\begin{array}{c} F0_{st}=12*log_{2}\left(\frac{F0_{Hz}}{F0_{mean}}\right), \end{array}$$
(1)
where *F*0_*mean*_ is the subject’s mean F0 aggregated over all F0 contours extracted from all of the subject’s utterances. This method of converting F0 into semitones has the benefit of partly cancelling out the large-scale, gender-based differences in voice pitch (males typically have lower voice pitch than females). The effect of sentence length on sentence-initial pitch peaks is expected to be smaller than the gender effect. When gender variation in voice pitch is included in the data, the critical effects of sentence length and WM may remain unrevealed.

#### Statistical analysis

The goal of the statistical analyses is to determine whether the scaling of sentence-initial pitch peaks in long sentences is affected by an independent effect of incrementality or by the simultaneous effects of incrementality and high mental load. As the manipulations of the factors Double Actor (agent vs patient) and Identity (same vs different) elicit short and long sentences (see in Materials), the combinations of these are reduced into a factor Sentence Length (short vs long) for the main analysis. Thus, the main analysis examines the effect of the interaction between Cognitive Load (low vs high) and Sentence Length (short vs long) on (i) the proportional duration of naming gazes at the first-mentioned actors, (ii) duration of naming gazes, (iii) the sentence-final pitch valleys, (iv) and the sentence-initial pitch peaks.

The four dependent variables (duration of naming gazes, proportional gaze durations, sentence-final F0 minima, sentence-initial F0 maxima) are modelled with separate linear mixed-effects regression analyses (LMER, as implemented in the *lme4* package in [82, 85]). All models include the interaction between Cognitive Load (low vs high) and Sentence Length (short vs long) as the fixed effect, the block and trial number as the covariate effects, and random intercepts and slopes for items and subjects. The analysis will be carried out using sum-to-zero coding of the fixed effects. To avoid the convergence issues, the models will be optimized following the procedures suggested in Bates et al. [82]. First, the continuous variables block and trial are centred and/or scaled for the statistical analyses. Second, the convergence tolerances are adjusted by applying an optimizing algorithm diverging from the standard test but which results in the converging model. Third, and only in case the previous measures do not yield the convergence of the model fit, the random effects structure will be simplified by removing the correlations term from the random effects structure. Finally, the significances of the model estimates are obtained with the help of the *lmerTest* package [86] in R [85]. The significances of the main effects and the interaction are determined at the threshold of p<0.05.

The first analysis tests the extent to which the proposed verb probe task tapped the conceptual retention. The proportional duration of naming gazes at the first-mentioned actors is assumed to increase under the high cognitive load. Thus, only the main effect of cognitive load is expected in this analysis. The second analysis investigates the absolute duration of naming gazes, as the interference effect may arise at the phonological planning stage (or semantico-syntactic encoding) instead. In particular, if the phonological encoding of the first-mentioned actors is disrupted due to the memorization of three words the duration of naming gazes right before the speech onsets should increase under the high cognitive load.

The third analysis checks the preliminaries of advance planning of sentence intonation. Namely, the aim is to test how constant the sentence-final low F0 is in the elicited sentences. For this, the statistical evaluation should find no effect of Sentence Length. Nevertheless, the sentence-final low F0 may increase under the high cognitive load, as the existing studies have reported generally higher and flatter F0 contours for speech under mentally challenging conditions [58–64].

Finally, the fourth analysis tests the effect of cognitive load on the scaling of sentence-initial pitch peaks. The significant interaction between Cognitive Load and Sentence Length should demonstrate that the degree of length-dependent pitch raise in sentence-initial pitch peaks depends on the cognitive load. If the cognitive load causes sentence planning processes to proceed incrementally and the incrementality of planning processes mainly bears on the scaling of the pitch peaks, then the sentence-initial pitch peaks are lower under the high load than under the low load, and the difference between the high and low load is greater in long sentences than in short sentences. If the incrementality and the high load both play a role in pitch scaling, then the tonal difference between the high and low cognitive load is expected to occur only in long sentences.

The exploratory analyses inspect the three-way interaction between the factors Double Actor (agent vs patient), Identity (same vs different) and Load (low vs high) on (i) the proportional duration of naming gazes at the first-mentioned actors (ii) and the sentence-initial pitch peaks. The first exploratory analysis of naming gazes aims to determine whether the pictorial scenes combining the similar and differing event participants either in agent or patient role would induce planning increments differing and gradually increasing in size. Known from the studies relying on the grouping effect (though with moving displays), the chunk conceptualized and planned before the speech onset increases together with the more complex phrase structures [37, 38]. The second analysis will assess whether the length-dependent pitch raising depends on the syntactic position of the length variation (as in [4]). If a large number of sentences will be uttered with a break between the subject noun phrase and the verb phrase, the desired significant interaction with Identity (i.e., Sentence Length) and Cognitive Load might only occur when Double Actor corresponds to the agent. The models of the exploratory analyses and the significance testing will follow the same procedures as described for the main analyses.

